### **4.3. Study Endpoint**

#### **4.3.1 Immunogenicity Endpoint:**

##### **Primary Endpoints:**

GMT and 4-fold rise of anti-SARS-CoV-2 neutralizing antibody 14 days after sequential vaccination of one booster dose;

GMT and 4-fold rise of anti-SARS-CoV-2 neutralizing antibody 28 days after sequential vaccination of one booster dose.

##### **Secondary Endpoints:**

GMT of anti-SARS-CoV-2 IgG antibody, 4-fold rise, GMI and proportions of neutralizing antibody titered  $\geq 1:16$ ,  $\geq 1:32$  and  $\geq 1:64$  before vaccination and 28 days after vaccination of sequential booster dose.

#### **4.3.2 Safety Endpoints:**

The incidence of any adverse reactions/events observed within 30 minutes after vaccination;

The incidence of adverse reactions/events observed within 0 ~ 7 days and 8 ~ 30 days after vaccination.

The incidence of SAEs observed up to 6 months after vaccination and full immunization.

#### **4.3.3 Immune Persistence Endpoints:**

GMT of anti-SARS-CoV-2 neutralizing antibody and IgG antibody, the proportions of neutralizing antibody titered  $\geq 1:16$ ,  $\geq 1:32$  and  $\geq 1:64$  at 3 months, 6 months, 9 months and 12 months after full course of immunization,

#### **4.3.4 Exploratory Endpoints:**

The vaccine efficacy of recombinant COVID-19 vaccine (CHO cells) against COVID-19, severe cases and deaths after 14 days following sequential vaccination in population aged 18 years and above.

### **4.4 Trial Hypothesis**

① The 4-fold rise of neutralizing antibody of recombinant COVID-19 vaccine (CHO cells) after sequential vaccination with one dose of vaccine is not inferior to that of inactivated COVID-19 vaccine (Vero cells), and the threshold of non-inferiority is -10%. If the lower bound of 95% CI is  $>-10\%$ , the hypothesis of non-inferiority in 4-fold rise between vaccine and control groups will be concluded.

② After sequential vaccination of one dose of recombinant COVID-19 vaccine (CHO cells),

GMT is not inferior to COVID-19 inactivated vaccine (Vero cells), and the non-inferior threshold is 2/3 (GMT ratio; the difference on log10 scale is -0.176). If the lower bound of GMT ratio 95% CI is  $> 2/3$ , the hypothesis of non-inferiority in GMT between vaccine and control groups will be concluded.

## 4.5 Safety Observation Indicators and Grading Criteria

### 4.5.1 Safety Observation Indicators

#### (1) Adverse events collected in 0-7 days

Local adverse events: pain, induration, swelling, rash, redness and pruritis.

Systemic adverse events: fever, diarrhoea, constipation, dysphagia, anorexia, vomiting, nausea, myalgia(systemic), arthralgia, headache, cough, dyspnoea, systemic pruritis (no skin damage), abnormal skin mucosa, acute allergic reactions, fatigue, and dizziness

Other adverse events: any medical events other than the above mentioned during clinical studies, such as acute diseases, accidental injuries, etc.

#### (2) Adverse events collected in 8-30 days

Any medical events, such as acute diseases and accidental injuries occurred during 8~30 days in clinical studies.

#### (3) Pregnancy events

Collect all pregnancy events and outcomes between vaccination and end of the study (6 months after full course of vaccination). Follow-up of the new-borns should last at least 30 days after birth.

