#### Safety Observation:

The subjects will be observed at the study site for 30 minutes after vaccination, and local and systemic adverse events will be collected. Within 0-30 days after vaccination, the local and systemic reactions of the subjects will be actively followed up and recorded on the vaccination diary card.

Serious adverse events (SAEs) need to be monitored from the first dose of vaccination and up to 6 months following the full course of immunization.

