## **7.3 Safety Observation and Follow-up**

### **7.3.1 Safety Observation**

(1) Observe the site for 30 minutes after vaccination to collect local and systemic adverse events.

(2) Telephone follow-up once in 6-24 hours after vaccination, within 1-3 days and 4-7 days respectively, the subjects were followed-up by telephone and guided to observe the adverse events

correctly and fill in the diary card.

(3) On the 14th day (Visit 4), the investigator reviews the filling of the diary card during this period and re-collect the diary card.

(4) On the 8th -30th day after vaccination, the investigator uses telephone follow-up once a week, combined with active report of the subjects to monitor the safety.

(5) When it is known that the subject has adverse reactions/events of Grade 3 or above, a face-to-face visit should take place within 24 hours.

(6) SAEs and AESIs are observed from the first dose to 6 months after the full course of vaccination by means of monthly telephone follow-up and self-reports from the subjects.

Note: Subjects should report respiratory tract infection symptoms such as fever and cough. Investigators should make comprehensive judgments, carefully identify whether it is common solicitation symptoms after vaccination or infection caused by other reasons, and closely observe the disease progress. Once the disease worsens, report it to the person in charge of the site quickly, and start the green treatment channel quickly to ensure that the subjects get timely diagnosis and treatment.

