## **7.8 Site Closure**

All subjects completed long-term safety observation for 6 months after vaccination and blood collection for 12 months after immunization. All original data are collated, entered, and verified and submitted to the statistician. After clarifying the data after blind audit by the statistician, the study site is closed.

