### **8.3 Handling and Reporting of Serious Adverse Events**

Serious adverse events refer to adverse medical events such as disability or loss of function, the need for hospitalization or prolonged hospitalization of subjects, and congenital abnormalities or birth defects.

Monitoring and reporting of adverse events in vaccine clinical trials are jointly completed by subjects, serious adverse event investigators, trial sites and responsible institutions at different observation time points with different stages.

The sponsor is the main body responsible for monitoring, evaluating and SAE reporting safety information of vaccine clinical trials. The person shall be designed as the administrator of clinical trial safety information monitoring and SAE reporting, and work with investigators to establish SOPs for clinical trial safety information monitoring and SAE reporting, know well the latest status of the safety information of the whole clinical trial, and timely report updates to all clinical trial institutions/ investigators and regulatory authorities.

If it is difficult to make a judgment on the correlation between SAE and vaccine or there is doubt about the judgment, when it is necessary to make a new judgment, the expert meeting shall make a judgment after argumentation.

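### The 6-month limit on pregnancy outcomes and SAEs ends before any term birth, and conflicts with the protocol's own newborn follow-up and 12-month study end

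*Protocol*

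**What the plan says.** - **Pregnancy collection**, Section 4.5.1 (3): "Collect all pregnancy events and outcomes between vaccination and end of the study (6 months after full course of vaccination". The sentence after it reads: "Follow-up of the new-borns should last at least 30 days after birth".
- **SAE window**, Section 4.2: "Serious adverse events (SAEs) need to be monitored from the first dose of vaccination and up to 6 months following the full course of immunization". Section 7.3.1 (6) gives the same limit and the method: "SAEs and AESIs are observed from the first dose to 6 months after the full course of vaccination by means of monthly telephone follow-up". Table 4 ticks SAEs at V1 to V7 only (V7 is the 6-month visit), and its monthly calls stop at 6 months.
- **SAE definition**, Section 8.3, includes "congenital abnormalities or birth defects".
- **End of follow-up**, Section 7.8: "All subjects completed long-term safety observation for 6 months after vaccination and blood collection for 12 months after immunization". The sample numbering rule in Section 7.4 puts the 6-month visit at D180 (+30 days) and the last one at D360 (+30 days). Table 4 still ticks contraception at V8 and V9.
- **Entry**: footnote 2 of Table 4 requires a negative pregnancy test in the 24 hours before vaccination. Section 5.1.1 admits only women who plan no pregnancy for 6 months.

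**The concern.** The two sentences of Section 4.5.1 (3) pull in opposite directions. The first stops the collection of outcomes at 6 months. The second presupposes that the mother is followed through delivery and the child for a month afterwards. The first also places the end of the study at 6 months, although visits continue to 12.

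The SAE window has the same difficulty. A birth defect counts as an SAE, but one first seen at a term delivery arises after the window has closed, and no sentence says how it is then reported.

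What is at stake is how completely and evenly outcomes are recorded. A site that applies the 6-month limit literally will record miscarriages and terminations but not term births. A site guided by the newborn sentence will record both. The resulting pregnancy table would be inconsistent between sites and weighted towards early losses, and it would say little about pregnancies that went to term.

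**Working it through.** The protocol gives no calculation here to reproduce. The check is date arithmetic against its own time limits.

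**Inputs from the protocol**
- Collection limit for pregnancy outcomes and SAEs: 6 months, taken as D180, or D210 at the end of the visit window.
- Last visit: D360, or D390 at the end of its window.
- Newborn follow-up: 30 days.
- Negative pregnancy test at D0.

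**Assumptions not in the protocol**
- Term is 37 to 42 weeks from the last menstrual period (LMP).
- Conception is about 14 days after LMP.
- An early pregnancy missed by the test has its LMP 28 days before D0, or 35 at the extreme.

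**Formula**: birth day = 7 × weeks − days from LMP to D0.

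| Case | 37 weeks | 40 weeks | 42 weeks |
|---|---|---|---|
| Conception on D0 (LMP D−14) | 259 − 14 = D245 | 280 − 14 = D266 | 294 − 14 = D280 |
| Missed at the test, LMP D−28 | 259 − 28 = D231 | 280 − 28 = D252 | 294 − 28 = D266 |
| Extreme, LMP D−35 | 259 − 35 = D224 | 280 − 35 = D245 | 294 − 35 = D259 |

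**Against the 6-month limit.** For conception on D0, term birth comes 245 − 180 = 65 to 280 − 180 = 100 days after D180, and 35 to 70 days after D210. The earliest entry in the table, D224, is still 44 days after D180 and 14 days after D210. A later conception moves the birth later by the same number of days. No term birth falls inside the limit.

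**What can fall inside it.** Gestation at D180 is (180 + 14)/7 = 27.7 weeks for conception on D0, and (180 + 35)/7 = 30.7 weeks in the extreme case. Losses, terminations, anomalies found before birth and very preterm births can therefore be recorded.

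**Against the newborn sentence.** For a term birth from conception on D0, the 30 days end at D245 + 30 = D275 to D280 + 30 = D310. This is past the 6-month limit but before D360. To finish the 30 days by D180, the birth would have to occur by D150, at no more than (150 + 14)/7 = 23.4 weeks for conception on D0. If the limit on outcomes binds, the newborn sentence has almost nothing to apply to.

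**Against the 12-month visit.** A birth at 37 to 40 weeks falls by D360 for conceptions up to D360 − 245 = D115 or D360 − 266 = D94. The newborn period is also complete by then for conceptions up to D85 or D64. Later conceptions within the first 6 months need contact after the subject's last visit. At the far end, conception on D180 gives a 40-week birth at D180 + 266 = D446 and newborn follow-up to D476.

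**The case against.** The strongest reply is that the passage can be read sensibly: the 6 months says which pregnancies are captured, and the newborn sentence, which has no cut-off, says how long they are followed. On that reading known pregnancies are followed past delivery. Section 8.3 supports it to a degree, since investigators must report any SAE within 24 hours of learning of it and must follow it until it resolves or settles. This is probably what was intended. But the first sentence limits outcomes as well as events, and neither it nor Section 7.3.1 (6) says that a birth defect first arising after 6 months is still reportable.

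Four stronger readings might be inferred, and the documents do not support them.

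- **That birth defects could not be observed at all.** Anomalies found before birth, terminations for anomaly and very preterm births can occur within 6 months, and newborn follow-up would reveal others.
- **That the protocol identifies a pregnancy risk of this vaccine.** It does not. Birth defects appear only within the general SAE definition, the list of events of special interest contains no pregnancy outcome, and no endpoint is specific to pregnancy.
- **That a calculable share of births is lost after the 12-month visit.** This would need a distribution of conception dates, which the 6-month pregnancy-planning restriction makes hard to assume. It would also need a cut-off for newborn follow-up that the text does not set. Section 7.8 closes a site only when all its subjects are complete, and Section 7.7 allows about 18 months for vaccination plus persistence follow-up, so many late births may precede closure.
- **That pregnancies first found at 9 or 12 months must be captured.** A 6-month capture window matches the pregnancy-planning restriction and the SAE window. Extending it is optional.

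**Conclusion.** The point holds as a contradiction in the text with a practical consequence. The 6-month limit on outcomes conflicts with the adjoining newborn sentence, and the 6-month end of study conflicts with follow-up to D360 (+30 days). Read literally, the outcome limit and the SAE window exclude all term births from conceptions at or after vaccination, by at least 65 days against D180 and 35 days against D210. They also exclude any birth defect first found at such a birth. Births from an early pregnancy missed at the test are excluded too, by at least 44 and 14 days.

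This rests on term being 37 to 42 weeks and on the negative test at entry. It does not depend on how many pregnancies occur, which the protocol does not estimate and which should be few. The sample size and the immunogenicity conclusions are unaffected. What is affected is the completeness and balance of pregnancy and birth-defect reporting.

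**What to change.** Reconcile the passages as follows.

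1. In Section 4.5.1 (3), make the 6 months define which pregnancies are captured, and remove it as a limit on their outcomes. Follow each captured pregnancy to its outcome, and each newborn for the 30 days already required.
2. In the same place, correct the parenthesis that puts the end of the study at 6 months. Call it the end of the safety observation period, with subject follow-up ending at 12 months.
3. In Sections 7.3.1 (6) and 8.3, state that a birth defect from a captured pregnancy is reported as an SAE even when found after 6 months. Because the SAE endpoint in Section 4.3.2 is an incidence up to 6 months, list such cases separately from that count.
4. In Section 7.8, allow pregnancy follow-up by telephone to continue after closure where needed.

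The cost is a wording amendment and a few telephone contacts for a small number of women. The drawback is that some reports may arrive after database lock and need a short addendum. Dosing, the visit schedule, the sample size and the main analyses do not change.

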### 4.5.2 Adverse Event Grading Criteria

Local adverse events, systemic adverse events, vital signs, and laboratory testing parameters after vaccination were determined based on the *Guiding Principles of Adverse Events Grading Criteria for Clinical Trials of Prophylactic Vaccines*.

**Table 2 Local Adverse Events Grading Table**

| Symptoms/signs               | Grade 1                                       | Grade 2                                                  | Grade 3                                                     | Grade 4                                             |
|------------------------------|-----------------------------------------------|----------------------------------------------------------|-------------------------------------------------------------|-----------------------------------------------------|
| Pain                         | Do not or slightly affect physical activities | Affect physical activities                               | Affect daily life                                           | Loss of basic self-care ability, or hospitalization |
| Induration *, swelling * * # | 2.5 ~ < 5 cm in diameter or 6.25 ~            | 5 ~ < 10 cm in diameter or 25 ~ < 100 cm  in | Diameter $\geq 10$ cm or area $\geq 100$ cm  or | Abscess, exfoliative                                |

|                     |                                                                                                      |                                                                                       |                                                                                                                                                                    |                                                                 |
|---------------------|------------------------------------------------------------------------------------------------------|---------------------------------------------------------------------------------------|--------------------------------------------------------------------------------------------------------------------------------------------------------------------|-----------------------------------------------------------------|
|                     | < 25 cm  in area not or slightly affecting daily life                                    | area or affecting daily life                                                          | ulceration or secondary infection or phlebitis or sterile abscess or wound drainage or seriously affect daily life                                                 | dermatitis, dermal or deep tissue necrosis                      |
| Rash *, flush * * # | 2.5 ~ < 5 cm in diameter or 6.25 ~ < 25 cm  in area not or slightly affecting daily life | 5 ~ < 10 cm in diameter or 25 ~ < 100 cm  in area or affecting daily life | Diameter ≥ 10 cm or area ≥ 100 cm  or ulceration or secondary infection or phlebitis or sterile abscess or wound drainage or serious affect daily life | Abscess, exfoliative dermatitis, dermal or deep tissue necrosis |
| Pruritus            | Itching at the vaccination site was relieved by itself or within 48 hours after treatment            | Itching at the vaccination site did not relieve within 48 hours after treatment       | Affect daily life                                                                                                                                                  | NA                                                              |

Note: \* In addition to measuring the diameter directly for grading evaluation, the progress and change of measurement results should also be recorded.

\*\* Maximum measured diameter or area shall be used.

# The evaluation and grading of induration and swelling, rash and redness should be based on the functional grading and actual measurement, with higher grading be selected.

When judging severity, it can be judged as a next grade adverse event only when it meets the grading criteria of the previous one.

**Table 3 Systemic Adverse Events Grading Table**

| Physical Sign                     | Grade 1                                                                                                       | Grade 2                                                                                       | Grade 3                                                                          | Grade 4                                      |
|-----------------------------------|---------------------------------------------------------------------------------------------------------------|-----------------------------------------------------------------------------------------------|----------------------------------------------------------------------------------|----------------------------------------------|
| Fever * (axillary temperature °C) | 37.3 ~ < 38.0                                                                                                 | 38.0 ~ < 38.5                                                                                 | 38.5 ~ < 39.5                                                                    | ≥ 39.5 for more than 3 days                  |
| Diarrhea                          | Mild or transient, 3 ~ 4 times/day, abnormal fecal characteristics, or mild diarrhea lasting less than 1 week | Moderate or persistent, 5 ~ 7 times/day, abnormal fecal characteristics, or diarrhea > 1 week | > 7 times/day, abnormal fecal characteristics, hemorrhagic diarrhea, orthostatic | Hypotensive shock, requiring hospitalization |

|                 |                                                               |                                                                                                           |                                                                                                   |                                                                               |
|-----------------|---------------------------------------------------------------|-----------------------------------------------------------------------------------------------------------|---------------------------------------------------------------------------------------------------|-------------------------------------------------------------------------------|
|                 |                                                               |                                                                                                           | hypotension, and electrolyte imbalance, requiring intravenous infusion > 2L                       |                                                                               |
| Constipation *  | Need fecal softener and dietary adjustment                    | Need laxative drugs                                                                                       | Stubborn constipation requires manual dredging or enema                                           | Toxic megacolon or intestinal obstruction                                     |
| Dysphagia       | Mild discomfort when swallowing                               | Restricted diet                                                                                           | Diet and conversation are very limited; can't eat solid food                                      | Can't eat liquid food; Need intravenous nutrition                             |
| Anorexia        | Loss of appetite, but no reduction in food intake             | Loss of appetite, food intake decreased, but body weight did not decrease significantly                   | Loss of appetite and obvious weight loss                                                          | Need measures to intervene (e.g., gastric tube feeding, parenteral nutrition) |
| Vomiting        | 1 ~ 2 times/24 hours without affecting activities             | 3 ~ 5 times/24 hours or limited activity                                                                  | > 6 times within 24 hours or intravenous rehydration is required                                  | hospitalization or other nutrition due to hypotensive shock                   |
| Nausea          | Transient (< 24 hours) or intermittent and normal food intake | Persistent nausea leads to reduced food intake (24 ~ 48 hours)                                            | Persistent nausea leads to almost no food intake (> 48 hours) or need for intravenous rehydration | Life Threatening                                                              |
| Myalgia (local) | not affect daily activities                                   | Slightly affect daily activities                                                                          | Severe myalgia, seriously affects daily activities                                                | Emergency or hospitalization                                                  |
| Arthralgia      | Mild pain without hindering function                          | Moderate pain, need analgesics and/or pain interferes with function, but does not affect daily activities | Severe pain, need for painkillers and/or pain affects daily activities                            | Disabling pain                                                                |
| Headache        | not affect daily activities and not need treatment            | Transient, slightly affect daily activities and may require treatment or intervention                     | Seriously affect daily activities and need treatment or intervention                              | Intractable, requiring emergency or hospitalization                           |

|                                                   |                                                    |                                                                                 |                                                                            |                                                                                                 |
|---------------------------------------------------|----------------------------------------------------|---------------------------------------------------------------------------------|----------------------------------------------------------------------------|-------------------------------------------------------------------------------------------------|
| Coughing                                          | Transient, without treatment                       | Persistent cough, effective treatment                                           | Paroxysmal cough, treatment uncontrollable                                 | Emergency or hospitalization                                                                    |
| Dyspnea                                           | Dyspnea during exercise                            | Dyspnea in normal activity                                                      | Difficulty breathing at rest                                               | Difficulty breathing, needing oxygen therapy, hospitalization or assisted breathing             |
| Pruritus at non-vaccination site (No skin damage) | Slight itching, not or slightly affects daily life | affects daily life                                                              | Itching makes it impossible for daily life                                 | NA                                                                                              |
| Abnormal Skin Mucosa                              | Erythema/pruritis/color                            | Diffuse rash/maculopapular rash/dryness/desquamation                            | Blister/exudation/desquamation/ulcer                                       | dermatitis involves mucosa, or erythema multiforme, or is suspected of Stevens-Johnson syndrome |
| Acute Allergic Reaction * *                       | Local urticaria (blister) without treatment        | Local urticaria, requiring treatment or mild angioedema, requiring no treatment | Extensive urticaria or angioedema requiring treatment or mild bronchospasm | Anaphylactic shock or life-threatening bronchospasm or laryngeal edema                          |
| Fatigue                                           | Not affect daily activities                        | Affect daily activities                                                         | Seriously affect daily activities and cannot work                          | Emergency or hospitalization                                                                    |

Note: \* Axillary temperature is usually used in China, tympanic temperature/temporal artery temperature = axillary temperature +0.5 °C. When persistent high fever occurs, the cause of high fever should be determined as soon as possible;

\* For constipation, attention should be paid to the changes before and after vaccination;

When judging severity, it can be judged as a next grade adverse event only when it meets the grading criteria of the previous one.

For clinical abnormalities not covered in the above table, the severity grading evaluation of adverse events should be carried out according to the following criteria.

| Grade 1                                                                                                     | Grade 2                                                                                                         | Grade 3                                                                                                          | Grade 4                                                                                                  | Grade 5 |
|-------------------------------------------------------------------------------------------------------------|-----------------------------------------------------------------------------------------------------------------|------------------------------------------------------------------------------------------------------------------|----------------------------------------------------------------------------------------------------------|---------|
| Mild: Short-term (< 48h) or slight discomfort, which does not affect activities and does not need treatment | Moderate: Mild or moderate activity restriction, which may require medical treatment, no or only mild treatment | Severe: obvious activity Restricted, need to see a doctor and receive treatment, and may need to be hospitalized | Critical: It may be life-threatening, severely limited in activities, and needs monitoring and treatment | Death   |

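### Table 3 gives no grade to a fever of 39.5 °C or more lasting 3 days or less, so a literal reading can leave it below Grade 3

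*Protocol*

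**What the plan says.** Section 4.5.2, Table 3, grades fever by axillary temperature. Grade 1 is 37.3 to below 38.0 °C, Grade 2 is 38.0 to below 38.5 °C and Grade 3 is 38.5 to below 39.5 °C, none with a duration. Grade 4 is "≥ 39.5 for more than 3 days", the only fever cell with a duration condition.

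Two notes under the table bear on this:

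- The step-up note says of an event that "it can be judged as a next grade adverse event only when it meets the grading criteria of the previous one".
- The fallback sentence, "For clinical abnormalities not covered in the above table", sends such events to a general severity scale. Its Grade 1 is "Mild: Short-term (< 48h) or slight discomfort, which does not affect activities and does not need treatment". Its Grade 2 allows mild or moderate restriction of activity with little or no treatment.

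In the vomiting row of Table 3, Grade 2 is "3 ~ 5 times/24 hours or limited activity" and Grade 3 is "> 6 times within 24 hours or intravenous rehydration is required".

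The grade is used in three places. Section 7.3.1 says that, for "adverse reactions/events of Grade 3 or above, a face-to-face visit should take place within 24 hours". Section 10.3.4 tabulates Grade ≥3 treatment-emergent events by group and compares the groups with Fisher's exact test. Section 7.6 suspends the trial if adverse reactions of Grade 3 or above exceed 15% of the subjects vaccinated in the subgroup.

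**The concern.** Grade 3 has a temperature ceiling of 39.5 °C, and Grade 4 adds a duration condition above that ceiling. A short fever above the ceiling therefore has no cell. No fever can have lasted more than 3 days on its first day, so every fever of 39.5 °C or more starts outside the table, including one that later becomes Grade 4. That is the period in which the 24-hour visit should be triggered.

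Applied as written, severity is inverted: 38.6 °C is Grade 3 at once, while 40 °C for one to three days has no stated grade. Such a fever could miss the urgent visit, the Grade ≥3 tables and, if vaccine-related, the 15% suspension count. Fever is a solicited event (section 4.5.1), so sites will grade it routinely.

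**Working it through.** **Step 1: place a test case.** Take 39.6 °C for one day.

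| Cell | Temperature condition | Duration condition | Met? |
|---|---|---|---|
| Grade 1 | 37.3 to <38.0 | none | no, too high |
| Grade 2 | 38.0 to <38.5 | none | no, too high |
| Grade 3 | 38.5 to <39.5 | none | no, too high |
| Grade 4 | ≥39.5 | more than 3 days | no, too short |

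The same holds for any temperature of 39.5 °C or more at any duration up to 3 days.

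**Step 2: apply the notes.** There are two readings.

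- *Cumulative.* The step-up note works for fever only if each lower bound counts as met by any higher temperature. Otherwise 38.2 °C would fail the Grade 1 range and could never be Grade 2. On this reading 39.6 °C for one day meets Grades 1 to 3, fails only the Grade 4 duration and is Grade 3.
- *Literal.* 39.6 °C is outside the Grade 3 range, so no cell covers the event. The grader goes to the general scale, which allows Grade 1 (under 48 hours, no effect on activities, no treatment) or Grade 2 (mild treatment).

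The table does not say which reading applies. The fever footnote deals with the measurement site and with finding the cause of persistent high fever; it assigns no grade.

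**Step 3: the vomiting row.** The Grade 2 count ends at 5 and the Grade 3 count starts above 6, so exactly 6 episodes in 24 hours has no count-based grade. The limited-activity and intravenous-rehydration limbs may still place it.

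**Step 4: size.** The protocol gives no rate for these fevers and no misgrading rate, so both are assumed. Let r be the proportion of subjects with a fever ≥39.5 °C for 3 days or less, and m the share of those left ungraded or graded below 3. Then p = r × m. Expected affected subjects are 300p per group, 900p per arm and 1,800p overall. The chance of at least one is 1 − (1 − p)^1800.

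| r | m | p | per 300 | per 900 | per 1,800 | P(at least one) |
|---|---|---|---|---|---|---|
| any | 0% | 0 | 0 | 0 | 0 | 0 |
| 0.1% | 10% | 0.01% | 0.03 | 0.09 | 0.18 | 0.165 |
| 0.1% | 50% | 0.05% | 0.15 | 0.45 | 0.9 | 0.594 |
| 0.1% | 100% | 0.1% | 0.3 | 0.9 | 1.8 | 0.835 |
| 0.5% | 50% | 0.25% | 0.75 | 2.25 | 4.5 | 0.989 |
| 1% | 50% | 0.5% | 1.5 | 4.5 | 9 | >0.999 |
| 1% | 100% | 1% | 3 | 9 | 18 | >0.999 |

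The row m = 0% is the case in which every grader reads cumulatively.

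**Step 5: the 15% rule.** Take the subgroup to be one group of 300. Then 0.15 × 300 = 45, so the rule is first exceeded at 46 (46/300 = 15.3%). With at most 3 cases missing, 46 − 3 = 43, so the rule could fail to trip only if the recorded count stood at 43 to 45.

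**The case against.** The strongest reply is that the ambiguity largely resolves itself. The step-up note is unworkable for fever unless the bounds are cumulative, and cumulative bounds give Grade 3. Fever is also the first row of Table 3, so it is hard to call it an abnormality the table does not cover. The fallback has an obvious purpose of its own: dizziness, for instance, is a listed systemic event with no row. Even on the general scale, an axillary 39.5 °C or more would rarely be free of any effect on activities or need for treatment, and the Grade 3 wording there is available.

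There are also safeguards. Section 7.3.1 provides "Telephone follow-up once in 6-24 hours after vaccination, within 1-3 days and 4-7 days respectively" and requires subjects to report fever, and section 7.2.1 allows recall for immediate evaluation. The Grade 4 suspension trigger is not affected. Both arms use the same table. Finally, section 4.5.2 bases the grading on an external guideline that is not reproduced in full; it may settle the case, and a local edit might depart from it.

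Most of this stands as a limit on the consequences. Grade 3 is the sensible grade, the rates in Step 4 are assumptions, and the upper end of the range needs every such case to be misgraded. It does not remove the defect. If fever counts as covered, the fallback is shut off and the event has no grade unless the grader infers one. Sites apply the table in this protocol, so a guideline outside it does not fill the gap. The vomiting point is minor: one integer, partly rescued by the other limbs of those cells.

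**Conclusion.** The concern holds. No cell in the fever row covers 39.5 °C or more for 3 days or less, and nothing else in the protocol assigns that event a grade. The likeliest outcome is that a careful grader infers Grade 3, in which case nothing is lost. A below-Grade-3 result is possible, not certain, and requires the literal reading plus the general scale.

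Under the assumed ranges, the Grade ≥3 rate is understated by 0.01 to 1 percentage point. The suspension rule would be affected only in a narrow band of counts. The event would still be recorded, and neither the primary endpoints nor the balance between arms is touched. What is at risk is a consistent grade for the highest short fevers and the actions tied to it. The effect is small, but the rule is faulty as written and should be corrected.

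**What to change.** In Table 3, define Grade 3 fever as 38.5 to <39.5 °C, or ≥39.5 °C for 3 days or less. With Grade 4 unchanged, every axillary temperature of 37.3 °C or more then falls in exactly one cell at any duration. Define Grade 3 vomiting as 6 or more times within 24 hours, keeping the intravenous-rehydration limb. Leave the step-up note and Table 2 as they are.

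The cost is two wording edits and a grading check in the eCRF, after comparing the new wording with the guideline cited in section 4.5.2. Section 7.2.1 already asks for daily temperatures for 7 days, so no new data are needed. Grade ≥3 counts and 24-hour visits may rise slightly. No Grade 4 cell changes, so the single-case suspension trigger becomes no easier to reach.
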